#### *Experimental group*

Subjects in this group will receive HCQ orally, 200 mg/day for 60 days. According to the result of the interim analysis at 4 and 8 weeks it will be decided whether to remove the blind and giving the prophylaxis to both groups or not. According to the results of the trial, an amend may be made to continue with an open label study, studying prophylaxis with HCQ.

#### *Control group*

Similar placebo for 60 days.

#### *Speed of recruitment*

All assigned workers will be recruited as they arrive to their work shifts.

#### *Start of recruitment*

Immediately after the revision process and, if applicable, approval of the protocol.

#### *Ending of recruitment*

#### *Tests to perform*

- Minimum tests at recruitment (before randomization) and at 30 and 60 days:
  - Blood count
  - Serum electrolytes
  - Blood chemistry (3 elements): to quantify the effects on blood sugar and rule out type 2 diabetes mellitus at baseline.
  - Hepatic profile
  - Electrocardiogram: to evaluate the incidence of heart conduction alterations.
- 10-respiratory virus and SARS-CoV-2 panel, only in case of symptoms.

At 30 and 60 days: surveillance of adverse events.

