## **Background**

The outbreak of respiratory infections due to coronavirus 2019 (COVID-19) began in China in December 2019, in the city of Wuhan, Hubei province (1 – 5). From this city, the outbreak has extended to other Chinese provinces and other countries (6). Until February 16, 2020, 28 countries had recognized confirmed cases, with 70,548 infections and 1,770 deaths in China and 413 infections in Japan (6). As other coronavirus, like SARS and MERS, the original human infection probably came from contact with animals, but effective transmission between humans has been proved, with a growth rate higher than 1 estimated at 2.6 (7) and a rapid duplication of cases that guarantees not only the continuation of the epidemics but its expansion, as has been observed so far.

COVID-19 has a wide range of clinical presentations, from asymptomatic infections to fatal disease with severe lung damage, respiratory failure and multiorgan failure. Severe damage has been associated, as in severe influenza, to a systemic

inflammatory reaction or cytokine storm, that may be attenuated by the immunomodulator effect of chloroquine or hydroxychloroquine. The fatality rate of COVID-19 has been estimated around 2%, but in severe cases with respiratory failure or need of intensive care it is considerably higher, between 10 – 15%, and could easily go up to 20 – 30% depending on the criteria of admission to an intensive respiratory care unit.

Until now there is no effective treatment for COVID-19 available, but it was recently reported that Remdesivir and chloroquine are effective in vitro. This one, in concentrations that can be obtained in vivo (8). Chloroquine and hydroxychloroquine (HCQ) are originally antimalarial drugs, almost identical chemically, that have been in regular use for decades, with a good security profile and accessible cost. The main toxicity of HCQ, investigational drug in this trial; is retinopathy, being its main associated risk factors doses higher than 5 mg/kg weight/day, lengthy use (longer than 10 years) and history of kidney failure, as well as use of tamoxifen. Other adverse effects reported with HCQ, happening scarcely, are alterations of heart conduction, cardiomyopathies, neurological symptoms such as nystagmus, headache, insomnia and nightmares, among others.

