## **Justification**

There is a lack of an approved pharmacologic treatment for chemoprophylaxis of COVID-19 and based on the in vitro effectivity of HCQ against the SARS-CoV-2 virus, its security profile and low cost we propose a randomized double blind controlled trial to evaluate the efficacy and security of HCQ to prevent symptomatic and severe infections in the healthcare workers highly exposed to COVID-19. The proposed dosage for prophylaxis is 200 mg/day. This is lower than 5 mg/kg/day in subjects who weight more than 50 kg, which makes the risk of retinal toxicity minimal, since subjects who weigh less than 50 kg will be excluded. In case of proving that the incidence of symptomatic and severe COVID-19 in health workers diminish significantly, this prophylaxis strategy may be one of the best tools to upkeep the security of the healthcare personnel exposed to COVID-19.

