### *Secondary outcomes*

1. Admission to the Intensive Respiratory Care Unit , need of invasive/non-invasive mechanical ventilation, death secondary to COVID-19, proved via PCR-TR according to the OMS protocol.
2. Incidence and severity of adverse events  
Adverse event: all medical events in the subjects included in the trial. The adverse event doesn't necessarily need to have a causal relation with the studied treatment. Examples of adverse events include abnormal symptoms and signs, hypersensitivity reactions or alterations in laboratory samples.  
Severe adverse event: defined as an event that results in the subject's death, in an event that threatens life, that requires hospital admission or causes incapacity.  
Due to the known effects of HCQ, special attention will be given to the incidence of the following adverse events:
  - a) Cutaneous reaction, generally when used along other drugs.
  - b) Medullar suppression, which must be watched over monthly through a control blood count.
  - c) Severe hypoglycemia, in which case the treatment must be suspended.
  - d) Proximal myopathy with proximal weakness or muscular atrophy.
  - e) Increase of suicidal risk according to the C-SSRS scale.

Adverse reactions are defined as the answer to a compound that is harmful and involuntary, that occurs at doses that normally are administrated to human beings. The described adverse reactions are:

- 1- 10% ophthalmologic, dose dependent.
- 2- Non-defined frequency: dermatologic, endocrine, metabolic, gastrointestinal, hematologic, hepatic, central nervous system, immunologic.

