### *Gradation of adverse reactions*

Grade 1: mild adverse event: refers to the effects that may happen due to the compound that are temporal and don't cause permanent harm or incapacity.

Grade 2: moderate adverse event; refers to the effects that may happen due to the compound that are temporal but require support from other therapeutics to be corrected and don't cause permanent harm or incapacity.

Grade 3: severe adverse event; refers to the effects that may happen due to the compound that might be temporal or permanent, without risk of mortality or incapacity.

Grade 4: adverse advent with risk of death or incapacity.

Evaluated through the following study:

Electrocardiogram: QT interval prolongation.

Blood count: bone medulla suppression, defined with the following values: neutrophiles < 500/microliters, platelets < 20,000/microliter, reticulocytes < 20,000 / microliter.

Hepatic failure: INR > 1.4, ALT > 33 units/liter, AST > 55 units/liter, total bilirubin > 4 mg/dl, platelets < 150,000/microliter.

Due to the nature of the study, having a captive population that comes to the INER at least five days a week, it is possible to estimate the number of days to the outcome. All participants will be instructed to notify the researchers in case of presenting cough, dyspnea or any other new sign or symptom. Weekly researchers will ask all included subjects about the symptoms associated with COVID-19, as well as any possible adverse events.

If any study subject presents adverse reactions, the treatment will begin immediately, and it will be notified at the same time. The initial treatment will be administered at the INER, support from other institutions will be requested, if necessary, without cost for the subject.

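### An ECG is taken before randomisation and at day 30, but no eligibility or individual suspension rule acts on its result

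*Protocol*

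**What the plan says.** The Protocol, Tests to perform, lists the ECG among the "Minimum tests at recruitment (before randomization) and at 30 and 60 days" and gives its purpose as "Electrocardiogram: to evaluate the incidence of heart conduction alterations".

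Two other sections show that the authors had a cardiac effect in mind. The Background lists, among other HCQ effects "happening scarcely, are alterations of heart conduction, cardiomyopathies". The section Gradation of adverse reactions includes the line "Electrocardiogram: QT interval prolongation", with no limit in milliseconds, no correction formula and no consequence.

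Other risks do carry rules. The Justification says of the dose that it is below the retinal threshold, "which makes the risk of retinal toxicity minimal, since subjects who weigh less than 50 kg will be excluded", and the Exclusion criteria add tamoxifen, reduced kidney function and retinopathy. Under Secondary outcomes one adverse event has an order attached: "Severe hypoglycemia, in which case the treatment must be suspended". For adverse reactions in general, the grading section says: "If any study subject presents adverse reactions, the treatment will begin immediately, and it will be notified at the same time". The next sentence there places that initial treatment at the institute, so it means care of the reaction, not a change to study drug.

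**The concern.** The pre-randomisation ECG is the one scheduled test that could identify a worker who already has the abnormality the Protocol intends to watch for. The Protocol orders the test and then gives the site no instruction on the result. The same holds at day 30: a newly prolonged QT would be recorded as an adverse event, but nothing says that dosing stops.

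What is at stake is participant safety and uniform handling between workers, not the error rate or the power. Rules on who may enter and when study drug stops belong in the protocol; an analysis plan would not supply them.

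**Working it through.** There is no figure in the Protocol to reproduce on this point. The check compares every place where the ECG, QT or cardiac conduction appears as a safety matter with every rule that could act on it.

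**Rules that act on the ECG**

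| Protocol section | What it acts on | Acts on the ECG? |
|---|---|---|
| Inclusion criteria | Age, exposed role with biosecurity training, no respiratory symptoms, consent | No |
| Exclusion criteria | Hypersensitivity, current HCQ or chloroquine, weight, pregnancy, lactation, liver, kidney, tamoxifen, retina and vision | No |
| Elimination criteria | Decision of the participant or legal representative | No |
| Secondary outcomes (suspension) | Severe hypoglycaemia | No |
| Gradation of adverse reactions | Care and notification of any reaction; QT listed without limit or action | No stop stated |
| DSMC section | Toxicity across the trial at interim review | Not for an individual |

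The number of eligibility or individual suspension rules that refer to the ECG is 0. The three eligibility lists show no break or redaction. A worker with an abnormal baseline ECG who meets the listed criteria is therefore eligible.

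**Timing.** Inputs: 60 daily doses (Experimental group), ECGs at baseline, day 30 and day 60 (Tests to perform). Share of the course before the first scheduled on-treatment ECG: 30/60 = 50%. The day-60 ECG coincides with the end of dosing. A suspension rule tied to scheduled ECGs therefore cannot protect the first half of the course; a baseline exclusion can.

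**How many workers.** The Protocol gives no prevalence, so 1%, 2% and 5% are assumptions. The total is 400, with 200 per group (Final calculation).

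| Assumed prevalence | Enrolled with the finding | Expected on HCQ (half) |
|---|---|---|
| 1% | 400 × 0.01 = 4 | 2 |
| 2% | 400 × 0.02 = 8 | 4 |
| 5% | 400 × 0.05 = 20 | 10 |

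**Screening cost of an exclusion.** Workers to screen = 400 / (1 − share excluded), rounded up.

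| Assumed share excluded | Calculation | To screen | Extra |
|---|---|---|---|
| 1% | 400 / 0.99 = 404.04 | 405 | 5 |
| 2% | 400 / 0.98 = 408.16 | 409 | 9 |
| 5% | 400 / 0.95 = 421.05 | 422 | 22 |

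**The case against.** The strongest reply is that the ECG does the job the Protocol gives it. Incidence cannot be measured without a baseline, and the blood count, electrolytes and hepatic profile are likewise taken at recruitment with no laboratory cut-off for entry. Marrow suppression is to be watched monthly, also with no suspension order. On this view the plan is consistent: eligibility rests mainly on history, weight and pregnancy status. That stands as far as it goes: the ECG is not unused, and the Protocol does not contradict itself. But liver and kidney disease at least have a history criterion, whereas the heart has neither a history nor a test criterion.

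A second reply is that the risk is small. The dose is low, the Background calls the cardiac effects scarce, workers are questioned weekly and told to report symptoms, and an independent committee reviews toxicity. This limits the weight of the point. It does not close the gap, because a symptom question does not detect a silent QT prolongation and the committee's review is at trial level.

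Some stronger readings are tempting, and the documents do not support them:

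- A reader might infer that a certain number of workers would be harmed. The Protocol gives neither a prevalence nor a cardiac event risk for workers with an abnormal baseline ECG.
- A reader might infer that day 30 is the only ECG that could ever change dosing. The tests are described as a minimum, so an earlier unscheduled ECG is not barred; day 30 is only the last scheduled one that can still affect dosing.
- A reader might infer that the site must continue HCQ despite an abnormal ECG. The text does not order a stop, but it does not forbid one.
- A reader might infer that an exclusion would erode the planned sample size. Exclusions happen before allocation, and the plan is to include 200 per group, so the cost is extra screening.

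**Conclusion.** The point holds as a gap in the safety rules. The Protocol recognises conduction alterations and QT prolongation as matters to watch, schedules the test at the right times, and states no rule that uses the result for an individual. Followed to the letter, the eligibility list admits a worker with a markedly abnormal baseline ECG, and a new abnormality at day 30 has no stated consequence for dosing.

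The only size taken from the document is that 50% of the doses precede the first scheduled on-treatment ECG. The 2, 4 or 10 workers expected on HCQ rest on the assumed prevalences of 1%, 2% and 5% and on equal groups, and they count workers exposed, not harms. Confidence is high that no rule is stated; the clinical consequence is not quantifiable from the document. No estimand, error rate or analysis is affected. This is a cheap improvement.

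**What to change.** 1. In Exclusion criteria, add: *pre-randomisation ECG, read before allocation, showing a QTc above the limit fixed in this protocol (correction formula named), or a clinically significant conduction disorder from the protocol's list.* The documents give no limit, so the sponsor must set the limit and a short named list before the first randomisation. Naming the disorders avoids excluding workers for trivial findings.
2. In Gradation of adverse reactions, add: *study drug is suspended if the day-30 ECG, or any unscheduled ECG during treatment, exceeds the same QTc limit or shows a new conduction disorder from the list; the subject stays in follow-up and in the intention-to-treat analysis.*

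The cost is Protocol wording and a requirement to read the baseline ECG before allocation; the ECGs are already scheduled. A few more workers must be screened to randomise 400 (5, 9 or 22 extra under the assumed exclusion rates), all from the staff of one institute. Any suspension shortens exposure for that subject and slightly dilutes the intention-to-treat contrast.

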#### Necessary number of subjects

#### *Significance level*

5% alpha at two tails.

#### *Power*

(1-beta, possibility of detection): 90%

### *Final calculation*

According to the proposed statistical analysis, the difference in time to outcome will be performed with a log-rank test, using the following formulas:

$$n = \frac{d}{2 - S1(\infty) - S2(\infty)} \text{ y } d = (Z\alpha(2) - Z1 - \beta)^2$$

Considering a difference of 10% of higher survival rates free of COVID-19 and considering a reported survival rate free of COVID-19 of 76%, a sample size of 159 per group is obtained. Considering the losses, it is decided that 200 subjects will be included per group, for a total of 400 subjects.

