## **Definition of the Problem**

Healthcare personnel have a high risk of COVID-19 infection (1). In China, until the beginning of March, more than 3300 COVID-19 infections in medical staff have been reported, and in some hospitals such as Clinic Barcelona 23% of physicians have contracted COVID-19. In Italy, the estimated incidence of COVID-19 is similar, with 20% of medical staff infected (1). Another severe problem is that healthcare workers may take the COVID-19 infection to their homes, having transmission to their family members been reported; besides, personnel might be an in-hospital vector, spreading the infection to patients being treated for other causes, or to the rest of the medical team.

Disease in healthcare personnel is an extremely severe problem in health emergencies, since it limits capacity of attention, weakens the workforce and diminishes motivation. In fact, in China 40,000 physicians were mobilized from other regions to support Wuhan and its province in the initial outbreak. Moreover, in Italy, news of hiring physicians from other countries like Cuba, China and Venezuela to support medical care of affected patients spread, since health systems were overwhelmed.

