#### Description of population

Healthcare workers from INER, in contact with the attention of COVID-19 patients, including medical personnel, nursing practitioners, and paramedics such as stretcher handlers and cleaning staff. The INER workers included will have taken training courses on the use of biosecurity protection, with the goal of lowering the risk of COVID-19 infection.

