### *Main outcome*

Symptomatic infection (dry cough with or without dyspnea, with or without fever) due to COVID-19 proved via PCR-TR according to the OMS protocol.

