### Inclusion and exclusion criteria

#### *Inclusion criteria*

- At least 18 years of age
- Being a healthcare worker exposed to respiratory disease due to COVID-19: medical personnel, chemists, nurse practitioners, cleaning staff, stretch workers, transportation workers, administrative personnel and respiratory therapy; with training in biosecurity measures and proper use of respiratory protection equipment to lower the risk of COVID-19.
- Absence of respiratory symptoms at the randomization and start of treatment/placebo.
- Informed consent, including randomization to any group.

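### The sample size rests on an unsourced 76% COVID-free control rate, and at none of the control rates the protocol names do 200 per group give the stated 90% power

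*Protocol*

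**What the plan says.** The Protocol's Significance level section sets "5% alpha at two tails", and its Power section sets 90%. The Final calculation section plans a log-rank comparison with a 10% gain in COVID-free survival and proceeds by "considering a reported survival rate free of COVID-19 of 76%, a sample size of 159 per group is obtained". It then enrols 200 per group, 400 in all, to cover losses. It calls the 76% a reported figure but gives no reference, endpoint or time point for it.

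The protocol's only infection proportions for health staff are in Definition of the Problem: "in some hospitals such as Clinic Barcelona 23% of physicians have contracted COVID-19" and "In Italy, the estimated incidence of COVID-19 is similar, with 20% of medical staff infected". These correspond to 77% and 80% COVID-free.

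The trial's own setting is described elsewhere:
- The main outcome is "Symptomatic infection (dry cough with or without dyspnea, with or without fever) due to COVID-19 proved via PCR-TR".
- Description of population says the workers "will have taken training courses on the use of biosecurity protection, with the goal of lowering the risk of COVID-19 infection", and Inclusion criteria repeats the training requirement.
- Randomization defines a high-risk stratum and a low-to-moderate-risk stratum; the latter includes cleaning and administrative staff.
- Treatment lasts 60 days, while Statistical analysis censors event-free subjects at three months and uses the hazard ratio as effect measure.

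**The concern.** The 24% control risk is the input from which the number of subjects is derived, and the protocol gives no ground for it. It lies above both rates that the protocol reports. It is not linked to symptomatic PCR-proven disease, to this mix of staff, or to day 60 or three months. The two background rates are no better anchored, since neither states how infection was ascertained or over what period.

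A log-rank test draws its power from the number of events and the hazard ratio, and both depend on the control rate. If the stated 90% is wrong at every rate the protocol names, readers and the monitoring committee would judge a non-significant result against a power the trial never had. This is not detail that can be left to an analysis plan: the protocol fixes the rate, the power and the number itself.

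**Working it through.** **Inputs.** Two-sided alpha 0.05 (z = 1.960) and power 90% (z = 1.282), from Significance level and Power. Control 76% and treated 86% COVID-free, 159 and 200 per group, from Final calculation. Alternative control risks 23% and 20%, from Definition of the Problem.

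**The plan's own figure first.** HR = ln(0.86)/ln(0.76) = 0.550, and (1.960 + 1.282)² = 10.507.
- Schoenfeld: events = 4 × 10.507/(ln 0.5496)² = 117.3, so 118; per group 118/0.38 = 311.
- Freedman: events = 10.507 × (1.5496/0.4504)² = 124.4, so 125; per group 125/0.38 = 329.
- Two proportions, unpooled: 10.507 × (0.24×0.76 + 0.14×0.86)/0.10² = 318.2 per group.

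The 159 is not reproduced. Half of 318.2 is 159.1, so a per-group number may have been taken as the total; that is an inference. The formula as it appears in the text has no hazard-ratio term, but a term could have been lost in text extraction, so nothing here rests on it.

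**Power of the planned numbers.** With control risk p, treated risk q and n per group, events d = n(p + q) and HR = ln(1−q)/ln(1−p).
- Schoenfeld power = Φ(|ln HR|·√d/2 − 1.960)
- Freedman power = Φ([(1−HR)/(1+HR)]·√d − 1.960)

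Worked case, 24% v 14%, n = 200: d = 200 × 0.38 = 76. Schoenfeld: 0.5986 × 8.718/2 − 1.960 = 0.649, giving 74%. Freedman: 0.2907 × 8.718 − 1.960 = 0.574, giving 72%.

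For HR 0.55 held, q = 1 − (1−p)^0.5496.

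| Control risk | Effect held | Treated risk | HR | Events (200/group) | Power, Freedman to Schoenfeld |
|---|---|---|---|---|---|
| 24% | both coincide | 14.0% | 0.550 | 76 | 72-74% |
| 23% | 10 points | 13.0% | 0.533 | 72 | 73-76% |
| 23% | HR 0.55 | 13.4% | 0.550 | 73 | 70-72% |
| 20% | 10 points | 10.0% | 0.472 | 60 | 79-83% |
| 20% | HR 0.55 | 11.5% | 0.550 | 63 | 64-66% |

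The table assumes that all 200 per group are followed. If losses reduce each group to 159 (1 − 159/200 = 20.5%), then at 24% v 14% d = 159 × 0.38 = 60.4 and power is 62-64%.

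**What drives the gap.** At the plan's own rate, power is already 16 to 18 points below 90%. Moving the control risk from 24% to 23% changes it by about 2 points. Moving to 20% raises it by about 8 to 9 points if the absolute difference is held, or lowers it by about 8 points if the hazard ratio is held. Holding 10 points at 20% means a 50% relative reduction, against 10/24 = 42% in the plan.

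**The case against.** Final calculation plans an absolute difference, and under that reading a lower control rate raises power. The background figures are illustrative, and the protocol does not say the 76% was taken from them, so an uncited third source is possible. The gap between 24% and 23% is trivial. All of this stands: the missing citation is a gap in documentation, not a contradiction, and the control rate alone does not produce a one-way power loss.

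A reader might infer more: that training, low-risk staff and a symptomatic-only endpoint must push the placebo rate below 20%, so that power collapses. At HR 0.55 and 200 per group, an assumed 15% would give 51-54% and an assumed 10% would give 37-39%. The documents do not support that as a finding:
- No rate below 20% appears in them.
- They do not say that the Barcelona or Italian staff were untrained, nor that those figures count asymptomatic infections.
- The general objectives target highly exposed workers, and one stratum performs intubation, bronchoscopy and critical care, which points the other way.
- The unstated time windows could move the rate in either direction.

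The direction is firmest for the endpoint. The Background says that infection can be asymptomatic, and virus testing is done only when there are symptoms. The size of that effect is unknown. Conversely, at an assumed 15% v 5% the power would be 91-95%, but only by assuming a 67% relative reduction.

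**Conclusion.** The point holds in a limited form. The 76% is unsourced, differs from the protocol's only reported rates, and is not shown to fit this endpoint, population and period. At the three control rates the protocol names, 200 per group give between 64% and 83% power on either reading of the effect, not 90%. At the plan's own 24% v 14% the figure is 72-74%, or 62-64% with 159 per group.

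It should not be read as showing that the control rate causes the shortfall: most of that comes from the 159, which is about half of the 311 to 329 required. Nor do the documents establish that the true placebo rate is lower than planned. The figures assume proportional hazards, 1:1 allocation, a single final test at two-sided 5% and, except where 159 is used, no losses.

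**What to change.** In the Power and Final calculation sections:
- Replace the 90% with the power that 400 subjects give at control risks of 24%, 23% and 20%, both with all 200 per group and after the allowed losses.
- Give a source or justification for the 76%. Use 77% and 80% COVID-free as sensitivity values, not as replacements, because they carry no endpoint definition or time window either.
- State whether the planned effect is the absolute 10-point difference or a hazard ratio of 0.55. The Hypothesis section's wording of more than 10% does not settle this.
- Name the time point, day 60 or three months, to which the control rate refers.
- Label any rate below 20% as an assumption.

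Do not add a check of the pooled event count at the 4-week look against 76 events. That total belongs to full follow-up of 400 subjects, whereas the look occurs when half the sample has four weeks. At constant hazard, the 200 followed subjects would yield 100 × (1 − 0.76^(28/T)) + 100 × (1 − 0.86^(28/T)) events: about 13 for T = 90 days and 19 for T = 60 days. Such a check would signal a shortfall even if 24% were right. No new reporting rule is needed either, since the hazard ratio with its 95% confidence interval is already planned.

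The cost is protocol wording and a recalculation, with no added subjects or visits. The only downside is a less favourable stated power.

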### Statistical analysis

Categorical variables will be described with frequencies and percentages, numerical variables with mean and standard deviation or median and interquartile range according to their distribution. The time to the outcome (COVID-19) and to the compound outcome will be estimated, in both the experimental and the placebo group. The survival function will be estimated with the Kaplan – Meier method and the log rank hypothesis test will be used to contrast the time to outcome in each study group. The hazard ratio and its 95% confidence interval will be used as measure of association strength to evaluate the effect of the prophylactic HCQ over the main and secondary outcomes of the study. The effect of prophylaxis on both proposed

study strata will be estimated with the log rank test, and the interaction prophylaxis – strata will be evaluated with Cox regression. Due to the urgency of knowing the study results, the following interim analysis are proposed: at the moment that the 50% of the sample has had a follow-up of four weeks and at the moment that 50% of the sample has had 8 weeks of follow-up. The subjects that do not present the outcome will be censored in their follow-up at three months from the random allocation and start of the intervention (HCQ/placebo). We propose a multivariate Cox analysis to evaluate the risks associated with COVID-19 and risk of the composite outcome. All analysis will be two-tailed, the analysis strategy is intention to treat, and all randomized subjects will be included in the analysis.

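### The stated 159 per group is about half of what the protocol's own assumptions require: power is about 62–64% at 159 and at most 72–74% at 200 per group, not 90%

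*Protocol*

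**What the plan says.** The design inputs are in the Protocol's section on the necessary number of subjects.

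- Significance level: "5% alpha at two tails".
- Power: 90% (printed as "1-beta, possibility of detection): 90"%).
- Test, under Final calculation: "the difference in time to outcome will be performed with a log-rank test".
- Effect, same place: "Considering a difference of 10% of higher survival rates free of COVID-19".
- Reference rate, same place: "considering a reported survival rate free of COVID-19 of 76"%.

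The section prints a formula that turns events into subjects, n = d/(2 − S1 − S2), and reports that "a sample size of 159 per group is obtained". It then adds: "Considering the losses, it is decided that 200 subjects will be included per group, for a total of 400 subjects". The loss rate is not given; 159/200 = 0.795 implies about 20.5%.

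The Statistical analysis section sets the end of follow-up: "The subjects that do not present the outcome will be censored in their follow-up at three months from the random allocation".

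**The concern.** A rise in COVID-free survival from 76% to 86% is a moderate effect on an outcome that most participants would not have. At 159 per group only about 60 events are expected in total, which is few for 90% power at a hazard ratio near 0.55. The stated sample size therefore looked too small for the stated error rates.

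The power figure tells ethics reviewers and the monitoring committee what the trial can show, and the Ethical considerations section rates the trial as above minimal risk. If the power is overstated, a null result will be given more weight than it deserves. Readers would take a 10-point benefit as ruled out with a 10% chance of error, when the chance of missing it is several times larger.

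**Working it through.** **Inputs (all from the Protocol).** Two-sided alpha 0.05, so z = 1.960. Power 0.90, so z = 1.2816. S1 = 0.76. S2 = 0.76 + 0.10 = 0.86; the 86% is not printed and reads the 10% as absolute percentage points. Equal allocation.

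**Common quantities**
- (1.960 + 1.2816)² = 10.507
- HR = ln 0.86 / ln 0.76 = 0.1508 / 0.2744 = 0.5496, and ln HR = −0.5986
- 2 − S1 − S2 = 0.38, the divisor in the protocol's own formula

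**Attempt to reproduce 159.** The formula for d, as it appears in the text at hand, contains only the z-values. With the z-values added it gives 10.507 / 0.38 = 27.7 per group. With the printed minus sign it gives (1.960 − 1.2816)² / 0.38 = 1.2 per group. Neither is 159. Symbols may have been lost when the PDF was read, so nothing below depends on this formula.

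**Required size at 90% power**

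| Method | Calculation | Events | n per group |
|---|---|---|---|
| Schoenfeld | d = 4 × 10.507 / 0.5986² ; n = d / 0.38 | 117.3 | 309 |
| Two proportions, unpooled | 10.507 × (0.76×0.24 + 0.86×0.14) / 0.10² | – | 318.2 |
| Freedman | d = 10.507 × (1.5496 / 0.4504)² ; n = d / 0.38 | 124.4 | 327 |

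A pooled two-proportion version gives 322, or 342 with continuity correction. The stated 159 is 49–51% of the three tabulated values.

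**Power of the stated and planned sizes.** Expected events are n × 0.38. Schoenfeld power is Φ(√(events/4) × 0.5986 − 1.960). Freedman power is Φ(√events × 0.4504/1.5496 − 1.960).

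| n per group | Events | Schoenfeld | Freedman | Simulated log-rank |
|---|---|---|---|---|
| 159 | 60.4 | Φ(2.326 − 1.960) = 64.3% | Φ(2.259 − 1.960) = 61.8% | 62.7% |
| 200 | 76.0 | Φ(2.609 − 1.960) = 74.2% | Φ(2.534 − 1.960) = 71.7% | 72.5% |

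The simulation used 20,000 trials per size with exponential event times. At 311 and 327 per group it gave 89.5% and 90.7%, so the formulas are sound here.

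**Difference detectable with 90% power, from 76%.** At 159 per group it is 89.1% (Schoenfeld, HR 0.42) to 89.9% (Freedman, HR 0.39), or 13–14 points. At 200 per group it is 88.0% to 88.5%, or 12–12.5 points.

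**Other readings of the 10% difference, at two-sided 5% and 90% power**
- 76% as the treated rate (66% v 76%): 421–433 per group
- 10% relative increase in survival (76% v 83.6%): 572–589 per group
- 10% relative reduction in risk (76% v 78.4%): more than 6,000 per group

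**Other error rates.** For 76% v 86%, a size of about 158 appears only with a one-sided 10% alpha and 80–85% power. That contradicts the Significance level and Power sections.

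**The case against.** The strongest reply is that the trial enrols 400, not 318. The Statistical analysis section includes all randomised subjects by intention to treat, and in a log-rank analysis people who leave early still contribute time and events until they are censored. To treat 200 as exactly 159 assumes that about 20.5% are lost and contribute nothing, and the protocol does not state a loss rate. This stands. The 62–64% is the value under the implied loss and 72–74% is the no-loss ceiling; with an assumed 10% loss (180 evaluable) the power would be about 67–70%. But the ceiling is still well below 90%, and the extra subjects were added to cover losses, not to supply power.

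Two further cautions are fair. First, the printed formula may have been damaged in reading, so its missing effect-size term is weak evidence. Second, the origin of 159 is not documented. Half of 318.2 is 159.1, which suggests that a per-group figure was taken as a total and halved. But half of the log-rank results would be 154 or 164, so this is a plausible inference and no more. The finding needs neither point, because it rests only on the stated rates and error levels.

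**Conclusion.** The concern holds. At two-sided 5% and 90% power, 76% against 86% needs about 310–330 per group before losses, so 159 is about half of what is required. The planned 400 subjects give between about 62% and 74% power depending on losses, which means a 26–38% chance of missing the assumed benefit.

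This rests on reading the 10% as absolute points, on proportional hazards, and on 76% applying at the end of follow-up. The other readings of the 10% enlarge the shortfall. Three calculation methods and a simulation agree closely.

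**What to change.** Correct the Power and Final calculation sections of the Protocol.

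1. State both survival rates (76% and 86%, if that is what was meant) and the implied hazard ratio of 0.55. If the source document's formula for d lacks the hazard-ratio term, print the full log-rank formula.
2. Replace 159 with the size that these inputs require: about 310–330 per group for 90% power, before losses. With the implied 20.5% loss this would be about 390–412 per group (309/0.795 = 389; 327/0.795 = 411; the upper end is after rounding up).
3. State the power of the size actually chosen: about 72–74% with 200 per group and no losses, falling to 62–64% if only 159 per group contribute. Equivalently, 90% power holds only for about 76% v 88–88.5% at 200 per group, or 76% v 89–90% at 159.
4. State the loss rate assumed.

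The cost is protocol wording and a less favourable power statement. No extra enrolment is needed to make the statement correct; if the sponsor wants to keep 90% power for a 10-point difference, the sample size would have to rise to the figures in item 2.
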